#### Exclusion criteria

The absence of an arterial catheter for blood sampling.Medical history of home mechanical ventilation which may lead to prolonged stay in the ICU, including long-term oxygen therapy and non-invasive ventilation not associated with sleep apnoea.Clinical conditions requiring treatment with extracorporeal membrane oxygenation (ECMO), that is, an inspired oxygen of 100% for more than 24 hours.Head trauma or other conditions where intracranial pressure may be elevated and tight regulation of arterial CO_2_ level is paramount.Primary (non-overdose related) neurological patients (Glasgow Coma Score 24).Severe heart failure classified by grade 4 American Heart Association guidelines.End-stage liver disease.Multiple ICU admissions within the medical stratification group, that is, more than one admission.Corrective orthognathic surgery.ICU admission following oesophageal surgery.Patients with morbid obesity defined as either body mass index (BMI)≥45; or BMI≥35 with an Acute Physiology and Chronic Health Evaluation II (APACHEII) score on admission >24.Pregnancy.Mechanical ventilation initiated for more than 24 hours in other centres.

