### Primary and secondary outcomes

The primary outcomes include:

Duration of mechanical ventilation to successful extubation defined as the time from the start of mechanical ventilation, defined as either the time of intubation in the ICU, or the time of admission to the ICU following previous intubation for surgery, and until successful extubation, with successful extubation defined as ≥48 hours of unassisted spontaneous breathing after extubation.

Unassisted spontaneous breathing is defined here to include supplementary oxygen and support with high-flow nasal catheters. Patients with non-invasive mask ventilation are considered to be assisted.

The secondary objectives of the trial are to compare the following variables in the standard care group and BEACON Caresystem group:

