Duration of mechanical ventilation to successful extubation following randomisation defined as the time from randomisation and until successful extubation, with successful extubation defined as ≥48 hours of unassisted spontaneous breathing after extubation.Time from control mode to support mode defined as the time following randomisation, from initiation of control modes of ventilation and until initiation of support modes of ventilation.Time from support mode to successful extubation defined as the time following randomisation, from initiation of support modes of ventilation and until successful extubation.Number of changes in ventilator settings per day defined as the daily registered number of changes to ventilator settings from randomisation until successful extubation.Time to first SBT defined as the time from randomisation to the first performed SBT.Time to first successful SBT defined as the time from randomisation to the first successful SBT.Time to first extubation defined as the time from randomisation to the first extubation attempt.Time to first disconnection from mechanical ventilation defined as the time from randomisation to the point at which mechanical ventilation is first discontinued.Percentage of time in control mode ventilation defined as the time from randomisation which is spent in controlled modes of mechanical ventilation in per cent of duration of mechanical ventilation.Percentage of time in support mode ventilation defined as the time from randomisation which is spent in support modes of mechanical ventilation in per cent of duration of mechanical ventilation.Use of sedatives defined as the cumulative use of sedative drugs from randomisation until successful extubation.Use of neuromuscular blockading agents defined as the cumulative use of neuromuscular blockading agents from randomisation until successful extubation.Number of intubation free days defined as the number of days without intubation from randomisation until successful extubation.Number of reintubations defined as the number of reintubations following extubation from randomisation until successful extubation.Number of tracheostomies defined as the number of patients having tracheostomy performed from randomisation until successful extubation or protocol end.Number of patients on prolonged mechanical ventilation defined as the number of patients on mechanical ventilation ongoing for more than 21 days after the start of mechanical ventilation.Number and types of adverse events related to mechanical ventilation defined as the incidence of adverse events directly related to mechanical ventilation.ICU mortality defined as the mortality from randomisation and until death or ICU discharge.Length of stay defined as the duration of ICU admission from the start of mechanical ventilation and until death or ICU discharge.Mobilisation times defined as the time from randomisation until (1) first mobilisation, for example, sitting on the edge of the bed, standing up and marching on the spot and (2) regaining independency, for example, able to drink/eat or comb hair.Daily patient physiological blood gas status defined as daily ABG values of SaO_2_, PaO_2_, PaCO_2_, pH from randomisation until successful extubation.Daily average physiological status defined as daily averages of measured values of oxygenation (SpO_2_), end-tidal CO_2_ fraction (EtCO_2_), ventilation (respiratory rate, tidal volume, anatomical dead space), pulmonary mechanics (airway pressure, respiratory system compliance) and ventilator settings as measured routinely at the bedside.

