
### Statistical considerations

Sample size was determined by a power analysis of duration of mechanical ventilation. Extrapolation of the 2016 ICU admission data from two London-based NHS hospitals provided a sample size of 548 patients over an 18-month period. In these patients, mean total duration of mechanical ventilation measured in days was 7.2, with an SD of 7.0 days. A study population of 137 patients in each randomisation group would allow detection of a 2 day or 30% improvement in the duration of mechanical ventilation in the BEACON Caresystem group assuming a similar improvement in SD, with an α level of 0.05 and power of 0.8. A 2 days or 30% reduction in duration of mechanical ventilation is similar to that used previously.^6^

Primary and secondary outcomes will be measured across the protocol duration and comparison made by independent samples t-test, or appropriate non-parametric testing if not normally distributed. Complementary analysis will be performed using Kaplan-Meier curves.

The study is not sufficiently powered to allow subgroup analysis for the groups specified in the randomisation strategy.

An independent data safety monitoring committee will be established as part of the study, with this committee responsible for defining stopping criteria. Safety data will be looked at after the first 80 patients have been recruited, with an interim analysis performed following 50% recruitment.

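### The primary outcome is tested without adjustment, although it contains recorded pre-randomisation ventilation time that treatment cannot change; this gives up some precision

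*Protocol article*

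**What the plan says.** The protocol article's Statistical considerations set one method for primary and secondary outcomes alike: "comparison made by independent samples t-test, or appropriate non-parametric testing if not normally distributed". The only addition is that "Complementary analysis will be performed using Kaplan-Meier curves". Neither uses covariates.

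Under Primary and secondary outcomes, the primary outcome is "Duration of mechanical ventilation to successful extubation defined as the time from the start of mechanical ventilation", running to successful extubation. The first secondary outcome is the same duration "defined as the time from randomisation and until successful extubation". Both start times must therefore be recorded for each patient. Other secondary outcomes are timed from randomisation by ventilator mode, including the share of time "which is spent in controlled modes of mechanical ventilation". The Study procedure section has the system collecting data in both arms.

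Patients enter only after at least 24 hours of invasive ventilation (Inclusion criteria), and no general upper limit is given. Randomisation is stratified by admission type, COPD and thoracic or non-thoracic diagnosis. Severity appears once, inside the obesity exclusion, as an "Acute Physiology and Chronic Health Evaluation II (APACHEII) score on admission >24".

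**The concern.** The interval from start of ventilation to randomisation is part of the primary outcome, is fixed before treatment begins and can vary between patients. A plain two-sample test counts that variation as noise. Mode at randomisation (control or support) is also known before treatment and plausibly predicts time to extubation.

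Precision matters here because the planning data are very variable: "mean total duration of mechanical ventilation measured in days was 7.2, with an SD of 7.0 days". The design has little power in reserve for a 2-day effect. Covariates that the trial already holds could recover some precision without more patients.

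**Working it through.** **Inputs from Statistical considerations.** Control mean 7.2 days and SD 7.0; 137 per group; a difference of 2 days or 30%; alpha 0.05 (taken as two-sided); power 0.80. The SD is assumed to improve similarly, so the intervention SD is 0.7 × 7.0 = 4.9 days.

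**The plan's own figure.** The claim is that "A study population of 137 patients in each randomisation group would allow detection of a 2 day or 30% improvement".
- With the averaged SD (7.0 + 4.9)/2 = 5.95: n = 2 × 5.95² × (1.960 + 0.842)² / 2² = 138.9, so 139 per group. This is within 3% of 137, and power at 137 is 79.4%.
- With separate SDs: n = (7.0² + 4.9²) × (1.960 + 0.842)² / 2² = 143.3, so 144 per group. Power at 137 is 78.2%.
- With separate SDs and 30% of 7.2 = 2.16 days: 123 per group. Power at 137 is 84.1%.

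The stated size is reproduced. For a 2-day effect, power sits just under 80%.

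**Effect of adjustment.** Unadjusted SE = sqrt((7.0² + 4.9²)/137) = 0.730 days. If baseline covariates explain a share R² of the variance in each arm, the SE is multiplied by sqrt(1 − R²). Power = Φ(2/SE − 1.96). The equivalent unadjusted size per arm is 137/(1 − R²). R² is an assumption; the document gives none.

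| Assumed R² | SE (days) | 95% half-width (days) | Narrower by | Power | Equivalent n per arm |
|---|---|---|---|---|---|
| 0 | 0.730 | 1.43 | – | 78.2% | 137 |
| 5% | 0.712 | 1.39 | 2.5% | 80.3% | 144 |
| 10% | 0.693 | 1.36 | 5% | 82.3% | 152 |
| 20% | 0.653 | 1.28 | 11% | 86.5% | 171 |
| 30% | 0.611 | 1.20 | 16% | 90.6% | 196 |

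**Pre-randomisation hours alone.** If they are independent of later duration, R² = SD(pre)² / [(7.0² + 4.9²)/2] = SD(pre)² / 36.5. An assumed SD of 1, 2 or 3 days gives about 0.03, 0.11 or 0.25.

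**Skewed durations.** For a non-negative duration, an SD close to the mean points to skew. The simulation used log-normal durations (mean 7.2, SD 7.0), a 30% reduction, 137 per arm, 4,000 runs per scenario, and a covariate explaining 10%, 20% or 30% of log-scale variance.
- t-test power 87/87/86%; linear adjustment 89/91/92%.
- Rank-test power 95/94/94%; rank ANCOVA 96/98/99%.
- Type I error 4.4% to 5.4%.

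The gain is therefore about 1 to 6 points, from a higher base than normal theory gives. Part of that higher base comes from using a 30% effect, which is slightly more than 2 days.

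**The case against.** The strongest reply is that this is a preference about efficiency. An unadjusted comparison of randomised arms is valid and unbiased, and its standard error already allows for chance imbalance. That stands. A reader might infer that the planned test is invalid or that the sample size is wrong; neither follows.

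The size is also uncertain. Patients are screened on ICU admission, and those ventilated for more than 24 hours in another centre are excluded. Both suggest a limited spread in pre-randomisation hours, so R² could be 5% or less, worth about 2 points of power. The non-parametric route may well be the one used, and the normal-theory figures do not describe it. The article does not mention a confidence interval. These points stand, and they are why the range starts at 5% and the simulated gains are shown beside it.

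A reader might also infer from the obesity exclusion that the trial holds APACHE II for everyone. The document does not show this: the score decides eligibility only when BMI is at least 35 and below 45. Mode at randomisation is not named as a baseline variable either, but the mode outcomes are timed from randomisation and the system collects data in both arms.

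Covariates are often left to an analysis plan, and one may exist here. But the article names its test, so an adjusted primary analysis elsewhere would depart from it. Nor does the randomisation-based secondary outcome answer the point. It removes the earlier hours, but it is secondary and has the same unadjusted test.

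**Conclusion.** The point holds as a loss of efficiency in a stated method. The case is firmest for hours ventilated before randomisation, because the outcome definitions make them both a component of the primary outcome and a recorded quantity.

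On normal theory with SDs 7.0 and 4.9 and a 2-day difference, the gain runs from about 2 points of power at R² of 5% to about 12 points at 30%. With skewed data it is about 1 to 6 points. All of this rests on an assumed R² and on a complete outcome. It would be tempting to quote the upper end as power the trial is known to be losing, but the document does not support any single figure.

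**What to change.** In Statistical considerations, prespecify the primary analysis as a regression of duration on arm, hours ventilated before randomisation and mode at randomisation (control or support), alongside the three stratification factors. Use robust standard errors, since the plan itself expects the SD to differ between arms. Fix this before any unblinded look at the data, including the interim analysis at 50% recruitment.

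- Add admission APACHE II only if it is recorded for all randomised patients.
- If the non-parametric route is taken, use a covariate-adjusted rank analysis such as rank ANCOVA. State that a proportional-odds model would estimate an odds ratio, not a difference in days.
- Keep the unadjusted comparison as a sensitivity analysis.

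The cost is a little more analysis work and, if APACHE II is used, entry of that score for every patient. No new patients are needed. Adjustment does not settle how patients who die or leave the ICU without successful extubation enter the outcome; that needs its own rule, and the adjusted model must suit it.

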## Safety, ethics and dissemination

### Adverse events

All adverse events will be monitored and documented until the end of study. Adverse events are reported to the trial sponsor according to their standard operating procedure for further investigation. As patients are critically ill, it is expected that unrelated adverse events will occur as part of hospital stay. Adverse events are therefore only defined in relation to changes in mechanical ventilation, for patients allocated to either the control or intervention arms.

Serious adverse events are defined as:Death, suspected to be caused directly by the settings of mechanical ventilation.Adverse events include the following events suspected to be caused directly by the settings of mechanical ventilation:Pneumothorax.Self-extubation.Hypoxaemia (SpO_2_ <90%; PaO_2_ <8.00 kPa).Alkalaemia (pH >7.5).Acidaemia (pH <7.2).

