### Intervention arm

Figure 2 illustrates the protocol flow in the intervention arm. At any time during the protocol, adverse events are addressed immediately, with a serious event resulting in exclusion from the study (illustrated as B in figure 2). Minor events are documented and the patient returned to the main protocol flow (illustrated at point A, at the top of figure 2). During intervention, the BEACON Caresystem can provide a number of different forms of advice to the user which require action. These are illustrated at the top of figure 2, and are described in turn below.

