#### Spontaneous breathing trial (SBT)

During weaning from mechanical ventilation, the BEACON Caresystem monitors the levels of Pressure Support (PS) and Positive End Expiratory Pressure (PEEP). When these levels are reduced to values below clinical guideline thresholds,^21^ the BEACON Caresystem automatically monitors variables evaluating spontaneous breathing criteria. If these remain within limits and for a duration determined by international guidelines,^21^ the system prompts the user to assess the appropriateness of extubation and provides a checklist to help. The primary function of the BEACON Caresystem with regards weaning is to reduce levels of support where possible; it does not suggest an active SBT or extubation. As such, the decision to extubate is according to standard clinical practice for both arms of the study, meaning that at any time the clinical team can perform an active SBT or extubate the patient without confirmation from the system. Reintubation is documented by the research team and the participant enters a standard care pathway, which involves the deactivation of the BEACON Caresystem. The participant is then followed up until the end of the protocol (figure 1).

The protocol ends with transfer or discharge from ICU or death (figure 1).

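### A serious adverse event is defined only as a death attributed to the ventilator settings, so a survived life-threatening event is not serious, and the intervention arm's serious-event rule is either without effect in a living patient or relies on a wider meaning that is not stated

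*Protocol article*

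**What the plan says.** Four parts of the protocol article bear on this point.

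- **Adverse events** (under Safety, ethics and dissemination) defines the serious category: "Serious adverse events are defined as:Death, suspected to be caused directly by the settings of mechanical ventilation". A separate list of adverse events suspected to be caused by the settings then names pneumothorax, self-extubation, hypoxaemia (SpO2 below 90%; PaO2 below 8.00 kPa), alkalaemia (pH above 7.5) and acidaemia (pH below 7.2). On reporting it says: "Adverse events are reported to the trial sponsor according to their standard operating procedure for further investigation".
- **Intervention arm** says that "adverse events are addressed immediately, with a serious event resulting in exclusion from the study", and then: "Minor events are documented and the patient returned to the main protocol flow". Both branches are said to be drawn in figure 2, which is not available here.
- **Spontaneous breathing trial (SBT)** sets the end of the protocol: "The protocol ends with transfer or discharge from ICU or death". For reintubated patients it provides a standard care pathway, "which involves the deactivation of the BEACON Caresystem. The participant is then followed up until the end of the protocol".
- **Primary and secondary outcomes** includes the safety outcome: "Number and types of adverse events related to mechanical ventilation defined as the incidence of adverse events directly related to mechanical ventilation". **Statistical considerations** adds: "Safety data will be looked at after the first 80 patients have been recruited".

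**The concern.** Seriousness normally separates events that threaten life from those that do not, whether or not the patient survives. Here survival alone takes an event out of the serious category. A tension pneumothorax that is drained in time, or profound hypoxaemia that is reversed, has the same status as a saturation just under 90% or a pH just past its limit.

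Two things are at stake. The first is the safety report: incidence by type does not distinguish a dangerous episode from one that barely crosses its threshold. The second is bedside conduct. The intervention arm has one rule for serious events and another for minor ones, and the text does not make clear which applies to a patient who survives a severe event suspected to be caused by the settings. This matters more because the Introduction says the commercial system had so far been evaluated only over 4 to 8 hours, whereas here it is used over the whole ICU stay. The article itself recognises that inappropriate settings can do serious harm and names lung damage.

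**Working it through.** The point concerns a definition, so the check is a comparison of the sections. The plan gives no figure to reproduce.

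**Step 1. What counts as serious.** The Adverse events section introduces its definition as a definition, not as examples, and gives one item: attributed death. The second list has five non-fatal event types. Three carry an entry threshold (hypoxaemia, alkalaemia, acidaemia) and two carry none (pneumothorax, self-extubation). None has a criterion that would raise it to serious. Count: one serious criterion, which is fatal; five listed non-fatal types, none of which can be serious.

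**Step 2. Apply that definition to the intervention-arm rule.** If the Intervention arm section uses the word in the same sense, only an attributed death triggers exclusion. The SBT section already ends the protocol at death, so the rule changes nothing for a living patient. Every survived event, however grave, then falls outside the serious branch. The only other branch named is for minor events, which returns the patient to the main flow and hence to system advice.

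**Step 3. Try the other reading.** The Intervention arm section speaks of a serious event, not a serious adverse event, so a broader bedside meaning may be intended. The rule then has a purpose, but its threshold is not stated, and the one definition the article does give is narrower. The term has two meanings in one document.

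**Step 4. Look for another stated route out of advice.** System malfunction sends the patient to standard care until the fault is corrected. Reintubation leads to deactivation of the system, with follow-up continued. Advice outside preset bounds, or about mode or sedation, prompts consultation with the clinician on duty. None of these clearly covers a survived severe event suspected to be caused by the settings.

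**Step 5. See what still captures such an event.** Adverse events are to be addressed immediately, monitored, documented and reported to the sponsor, and they are counted by type as a secondary outcome. The safety considerations provide continuous pulse oximetry with an alarm at SpO2 of 90% or less, continuous capnography and continuous peak-pressure monitoring, and the effects of advice can be reviewed in cases of doubt. What is missing is the severity label and the action attached to it; the event itself is recorded.

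**The case against.** The strongest reply has four parts.

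1. **Figure 2 may resolve the routing.** It illustrates both branches and cannot be seen. This stands in part: the article cannot be said to lack a workable rule, only that its text does not state one clearly. The definition is in the text and does not depend on the figure.
2. **Severity grading may sit in the sponsor's procedure, the case report form or the full protocol.** This stands for grading in general, and the absence of a definition of minor should carry little weight alone. It does not rescue the serious category: the article cites the procedure for reporting and investigation, and defines seriousness itself.
3. **The safety look is not limited to serious events.** This stands. A reader might infer that the 80-patient look could be blind to harm because the serious category may be empty. With about 40 patients per arm (assuming equal allocation) and an assumed attributed-death rate of 1%, the chance of no serious event in the device arm is 0.99^40 = 0.67. But the look covers safety data generally, and the independent committee sets its own stopping criteria, so that figure does not show that harm would be missed.
4. **Any gain in statistical detection rests on invented rates.** This also stands. With 137 per arm and a two-sided Fisher exact test at 0.05, power for separately counted severe events is about 75% if the rates are 2% and 10%, but only 27% at 2% and 6%. The documents give no rates and claim no power for safety comparisons, so the point should not rest on power.

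Two further inferences are tempting. One is that severe events are lost or that patients are locked into advice. The text contradicts this: events are recorded and reported, clinicians make every change to the ventilator, and they may extubate at any time; the article calls application of advice mandatory but expects that it will not always be applied. The other is that exclusion removes attributed deaths from the intervention arm's analysis. The article does not say whether exclusion means leaving the intervention or leaving the analysis, so this cannot be asserted.

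**Conclusion.** The point holds in a limited form. By the article's own definition, a survived life-threatening event caused by the ventilator settings is not serious. The intervention-arm rule for serious events is then either without effect in a living patient or based on a meaning the article does not give. Both readings call for a correction, and the unavailable figure can decide only which applies. This is a stated rule that is badly fixed; it does not depend on detail that an article would leave to a fuller document.

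The consequence is modest: severity is misclassified in safety reporting, and no clear stated rule says when to stop advice after a survived severe event. The conclusion rests on the text alone and needs no assumed event rate. The sample size, the alpha level and the planned primary comparison are unaffected. The change is worth making because it is cheap and bears on patient safety.

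**What to change.** Amend two sections together.

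- **Adverse events:** extend the serious category, in both arms, from attributed death to settings-related events that are life-threatening or need urgent intervention.
- **Intervention arm:** use the same term. Replace exclusion with pausing or stopping BEACON advice, giving standard care, and continuing follow-up and analysis in the randomised group, as the SBT section does for follow-up after reintubation. Bring figure 2 into line if it differs.
- **Reporting:** show serious events by arm at the 80-patient look and in the final report, beside the counts by type.

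The two wording changes must go together. Widening the definition alone would make the existing exclusion rule apply to surviving patients, and that rule is stated only for the intervention arm. In the control arm only classification and reporting change.

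The cost is a wording amendment, with no new committee, visit or procedure. There will be more serious-event reports in both arms. Device-arm patients whose advice is stopped will receive less of the intervention while remaining in their group, which slightly dilutes the treatment contrast.

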The results of this study compare care provided with the system’s advice with current clinical practice at study sites. As there is no standard of care or usual method of weaning in the UK, this study does not compare the system’s advice with that of best practice defined by clinical guidelines. To avoid comparing two interventional changes, no attempt will be made to standardise care in the control arm according to best practice.

As patients are studied for many days, it is not possible to store continuous waveform data for all patients at all times. Systematic analysis of patient-ventilator asynchrony will not therefore be possible.

This study excluded patients if ventilated for <24 hours. In doing so, patients ventilated post surgery defined previously as simple to wean are not included. This should not imply that the patients studied here are necessarily difficult to wean, but rather that they represent a broad cross section of mechanically ventilated patients not simply recovering from the effects of anaesthesia.

In addition, it is important to note that substantial training has been provided to all sites in the use of the BEACON Caresystem and the same clinical team treat patients for both the control and intervention arm. It is possible then that both training and use of the system influence routine care, potentially biasing study results.

This paper describes the study protocol of a randomised control trial evaluating the advice of the BEACON Caresystem in a general medical ICU population. This protocol represents an important step evaluating the use of advice over the whole of the ICU stay, and only in patients intubated greater than 24 hours. The results will indicate whether the BEACON Caresystem is a useful tool in optimising ventilation strategy.

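### The adverse-event outcome counts objective events only when the ventilator settings are suspected as the cause, so this one comparison can be biased by attribution that differs between arms

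*Protocol article*

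**What the plan says.** The Adverse events section of the protocol article opens broadly: "All adverse events will be monitored and documented until the end of study". It then explains that unrelated events are to be expected in critically ill patients, and narrows the term: "Adverse events are therefore only defined in relation to changes in mechanical ventilation, for patients allocated to either the control or intervention arms".

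Two definitions follow. The only serious adverse event is "Death, suspected to be caused directly by the settings of mechanical ventilation". The non-serious list is introduced by "Adverse events include the following events suspected to be caused directly by the settings of mechanical ventilation" and has five items: pneumothorax, self-extubation, hypoxaemia (SpO2 below 90%, PaO2 below 8.00 kPa), alkalaemia (pH above 7.5) and acidaemia (pH below 7.2). On handling, the section says "Adverse events are reported to the trial sponsor according to their standard operating procedure for further investigation".

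Under Primary and secondary outcomes, the adverse-event outcome has the same limit: it is the "incidence of adverse events directly related to mechanical ventilation".

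On who knows the allocation, the Study procedure section has the clinical team apply the system's advice in the intervention arm and switches the advice off in the control arm. The Discussion adds that "the same clinical team treat patients for both the control and intervention arm". The trial is called single-blinded, but the blinded party is not named.

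On monitoring, Statistical considerations says "Safety data will be looked at after the first 80 patients have been recruited", with an interim analysis at 50% recruitment.

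**The concern.** Each of the five listed events can be established without an opinion about its cause. The definition adds one: the event counts only if someone suspects that the settings directly produced it. That opinion bears on the very thing that was randomised. In one arm the settings follow the device's advice; in the other the team chooses them itself. Staff might be slower to blame their own choices, or quicker to blame a new device, or readier to excuse a device they were trained on. The direction cannot be predicted, but there is no reason to expect equal attribution in the two arms.

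The opening sentence does not remove the problem. Under the narrowed definition an event that nobody suspects is not an adverse event, so it need not be documented as one. Investigation by the sponsor comes after reporting and cannot restore events filtered out before it.

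At stake is the interpretation of the trial's one defined adverse-event outcome. A difference could reflect attribution alone, and a true excess could be hidden.

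**Working it through.** No figure in the article is in dispute, so the check has two parts: which safety comparisons depend on attribution, and how much differential attribution could matter.

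**1. Which comparisons depend on attribution** (definitions under Primary and secondary outcomes and Adverse events)

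| Event | Counted only if settings are suspected | Compared elsewhere without attribution |
|---|---|---|
| Pneumothorax | yes | no |
| Self-extubation | yes | no |
| SpO2 below 90% | yes | daily average SpO2 only, which can miss short falls |
| PaO2, pH thresholds | yes | daily blood gas values |
| Death | yes, as a serious adverse event | yes, ICU mortality from any cause |
| Reintubation | not a listed adverse event | yes, number of reintubations |

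For pneumothorax and self-extubation, the attributed count is therefore the only listed comparison. For blood gases and SpO2 there is a partial substitute, and for death a full one.

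**2. Illustration of size**

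Input from the article: n = 137 per arm (Statistical considerations). Assumed: the true proportion p of patients with a listed event, and the proportion a of those events attributed to the settings.

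Recorded patients per arm = n × p × a. With equal p, the ratio of recorded counts is the ratio of the two values of a.

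*No true difference, p = 20% in both arms* (137 × 0.20 = 27.4 per arm):
- a = 30% v 50%: 27.4 × 0.30 = 8.2 and 27.4 × 0.50 = 13.7; ratio 1.67, or 0.60 if reversed.
- a = 20% v 60%: 27.4 × 0.20 = 5.5 and 27.4 × 0.60 = 16.4.

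The recorded proportions are 0.06 v 0.10 in the first case and 0.04 v 0.12 in the second, with mean 0.08 in both. The standard error is √(2 × 0.08 × 0.92 / 137) = 0.0328. So z = 0.04 / 0.0328 = 1.22 (two-sided p about 0.22) in the first case and z = 0.08 / 0.0328 = 2.44 (p about 0.015) in the second.

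*Chance of a nominally significant false difference* (two-proportion test, two-sided 0.05, 137 per arm, equal true rates):

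| True rate, both arms | Attribution | Recorded | Chance |
|---|---|---|---|
| 20% | 50% v 40% | 14 v 11 | 8% |
| 20% | 50% v 30% | 14 v 8 | 23% |
| 20% | 50% v 25% | 14 v 7 | 35% |
| 40% | 50% v 40% | 27 v 22 | 14% |
| 40% | 50% v 25% | 27 v 14 | 64% |

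*A true difference hidden*: a doubling from 20% to 40% would be detected with about 95% power if every event counted. With attribution of 50% and 25%, the recorded proportions are 0.20 × 0.50 = 0.10 and 0.40 × 0.25 = 0.10, and the difference is gone.

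**The case against.** The strongest reply is that the restriction is deliberate and much of safety lies outside it. In critically ill patients most such events come from the illness, and the rule is worded identically for both arms. ICU mortality from any cause is a secondary outcome, as are reintubations, daily blood gases and daily average SpO2. This stands. A reader might infer that the whole safety comparison rests on unblinded opinion, or that deaths not blamed on the settings go uncompared; the documents support neither. Such deaths fall outside the serious-adverse-event label but inside ICU mortality.

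Second, nobody is named as the assessor of cause. The sponsor investigates reported events, a data safety monitoring committee is planned, and blinded assessment could be described in a document not shown. This stands in part. That the assessor knows the allocation is an inference, though a strong one where the bedside team raises the suspicion. The article does fix the counting rule, and later review cannot recover events never reported.

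Third, a reader might infer that the review after 80 patients would see only attributed events. The article does not say what those safety data contain, so that cannot be concluded.

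Fourth, the illustration rests on assumed rates and has no known direction. Its 30% v 50% case is not nominally significant, and at about 40 patients per arm the same assumptions give only 40 × 0.20 × 0.30 = 2.4 v 40 × 0.20 × 0.50 = 4 events. This is correct, and limits what the illustration can show.

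Finally, counting every threshold crossing would bring in a bias of its own. The section on sampling and measurement of blood gases says the system may require samples beyond clinical practice, and expects its requirement to be at most 6 a day in the intervention group. More samples find more crossings. This stands and shapes the fix.

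**Conclusion.** The point holds for the adverse-event and serious-adverse-event definitions and for the secondary outcome built on them. As written, the rule makes the count of objective events depend on a judgement about the randomised component of care, in a setting where the treating team knows the arm and no blinded adjudication is described. The resulting bias can go either way. It matters most for pneumothorax and self-extubation, which have no other listed comparison.

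The primary outcome and the attribution-free secondary outcomes are not affected. The size is unknown, because the article gives neither event rates nor attribution rates; the figures show only that a spurious or a masked difference is possible under plausible assumptions. The conclusion also assumes that the suspicion arises with people who know the allocation, which the article implies but does not state. The change is worth making because it is cheap and the outcome is hard to interpret without it.

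**What to change.** In Primary and secondary outcomes and in Adverse events:

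- Record every pneumothorax and self-extubation from randomisation to the end of protocol, in both arms, whatever the suspected cause.
- Keep suspected causation by the ventilator settings as a separate field. Compare all occurrences first and show the attributed subset second.
- Count SpO2, PaO2 and pH threshold events regardless of attribution as well, but compare them on a basis that does not depend on sampling frequency: for example, patients with a crossing on a common daily blood gas, or a rate per sample.
- Limit any SpO2 taken from the device to the period when it is active, since it is deactivated after reintubation.

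In Statistical considerations, state that the 80-patient review and the 50% interim analysis include all-cause ICU deaths by arm, which are already collected.

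The cost is a reworded definition, one extra case-report field, and a longer event listing in which most entries will reflect the underlying illness. No procedure or patient is added and no treatment changes.
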